#### **Analyses of secondary outcomes:**

Analysis of secondary outcomes (willingness to treat and harm reduction knowledge and attitudes) between the two arms will follow the same analysis approach as above.

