## Section 4: Protocol Synopsis

### 4.1 Study Design

#### 4.1.a. Detailed description

Rural counties, particularly in Appalachia, are battling fast-growing outbreaks of HIV. One of the most promising mechanisms for reducing HIV transmission in these communities is the use of buprenorphine which treats opioid use disorder and also decreases HIV risk. Despite the potential benefit of buprenorphine, health care professionals (HCPs) in rural areas of the United States are much less likely to have received the training and federal waiver necessary to prescribe this medication. The single biggest obstacle to extensive MOUD use is stigma—stigma among communities, families of people who use drugs (PWUD), and remarkably, among HCPs.

We recently completed a study demonstrating that OUD-related stigma is common among physicians in Ohio. This stigma is greater among physicians practicing in rural areas—the same areas experiencing the greatest impact of the opioid crisis. Stigma is also associated with fewer buprenorphine prescribers, syringe service programs, and naloxone dispensaries in the surrounding county. Physicians' stigma toward PWUD is predicted by 3 key attitudes that are unique to the opioid crisis and which require tailoring of existing training interventions.

Rural health care professionals would benefit from brief stigma-reduction training interventions but to date effective stigma-reduction interventions have not been tailored specifically for MOUD or for the rural primary care setting. Adapting MOUD-specific interventions that are feasible and acceptable for health care professionals practicing in rural areas is critical for improving access to buprenorphine in underserved rural communities.

This study includes developmental activities aimed at isolating the modifiable features of OUD-related stigma among rural health care professionals, adapting a brief stigma-reduction training intervention and finalizing the intervention with health care professional feedback, and implementing a two-arm randomized pilot trial among rural health care professionals to assess feasibility and acceptability of the intervention. We hypothesize that the brief stigma-reduction training intervention will be both feasible and acceptable in the rural primary care setting. Our specific aims are to:

Aim 1: Examine HCP knowledge and attitudes about OUD to understand their reluctance to prescribe MOUD and manage patients with OUD.

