|-----------|--------------------------------------------|----------|-------------------------------------------------------------------------------------------------------------------------------------------------------------------|
|           |                                            |          | follow-up cluster randomized trial to test intervention effectiveness.                                                                                            |
| Secondary | Training and prescribing waivers           | 6 months | Whether the participant completed any additional training (yes/no) and whether the participant received an X-waiver (yes/no)                                      |
| Secondary | Prescribing knowledge                      | 6 months | Knowledge of buprenorphine standards of care                                                                                                                      |
| Secondary | Willingness to work with patients with OUD | 6 months | 5-item scale ( $\alpha=0.87$ ) assessing willingness to work with patients with OUD.                                                                              |
| Secondary | Attitudes toward patients with OUD         | 6 months | 10-item scale ( $\alpha=0.81$ ) assessing bias toward patients with OUD, adapted from a previously validated scale measuring bias toward people who inject drugs. |

Subject participation duration: 24 months

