#### **Analyses of primary outcomes:**

Buprenorphine prescribing outcomes.

We will apply a generalized linear mixed model (GLMM). The GLMM will include subject ID as a random effect and clinic as a fixed effect; the appropriate link function will be used, invoking generalized estimating equations (GEE) to account for the longitudinal (repeated measures) aspect of the data. Using GEE accounts for the repeated-measures design and uses all available data, including participants who may have missed time points and accounts for the correlation between repeated outcome measures at two time points (at 3 and 6 months). We will specify a Gaussian error distribution and identity link to compare the means of each feasibility outcome between the two arms. The primary model will estimate effects across all time points; a secondary model will include an interaction term with time to estimate effects at 3 and 6 months separately.

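### The secondary-outcome analysis does not match the listed secondary outcomes, gives no explicit model for the two yes/no items, and sets no baseline restriction for the waiver outcome

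*Combined protocol and SAP*

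**What the plan says.** The Outcome Measures table of the combined protocol and SAP has four secondary rows, all timed at 6 months, holding five items:

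- Training and waivers: "Whether the participant completed any additional training (yes/no) and whether the participant received an X-waiver (yes/no"). These are two separate binary items.
- Prescribing knowledge: "Knowledge of buprenorphine standards of care".
- Willingness: a 5-item scale "assessing willingness to work with patients with OUD".
- Attitudes: a 10-item scale "assessing bias toward patients with OUD, adapted from a previously validated scale measuring bias toward people who inject drugs".

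The section on analyses of secondary outcomes is one sentence. Its subject is "Analysis of secondary outcomes (willingness to treat and harm reduction knowledge and attitudes) between the two arms", and it refers the reader back to the method given for the primary outcomes.

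The approach it points to, under the analyses of primary outcomes, is a mixed model combined with GEE. Clinic is a fixed effect and the outcome times are 3 and 6 months. That paragraph first promises whatever link function suits, then states: "We will specify a Gaussian error distribution and identity link", in order to compare means of the feasibility outcomes between arms.

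On waivers, Section 4.1.a describes rural clinicians as "much less likely to have received the training and federal waiver necessary to prescribe this medication". The eligibility text in the same section excludes only those already prescribing at full capacity.

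**The concern.** The two lists define what will be tested, and they disagree. An analyst who follows the analysis sentence would report on harm reduction, which has no instrument or time frame anywhere in the documents. The same analyst would have to decide, possibly after seeing data, whether and how to test training, waiver and perhaps the knowledge and attitude scales. The Initial Data Inspection section says that analysis details follow for each hypothesis; for training and waiver none follow.

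The waiver outcome has a further problem. The final training module links directly to waiver certification, so the effect of interest is on new waivers. Clinicians who already hold one contribute no information on that effect but stay in the denominator.

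The trial is meant to inform a larger one. If it is unclear which secondary outcomes were prespecified, or if the waiver contrast is diluted by an unknown amount, these estimates are less useful for that purpose.

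**Working it through.** The plan gives no figure for this point to reproduce. Its 80% power at d = 1.01 concerns the primary outcomes and is not affected.

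**1. Matching the lists.** The five table items are set against the analysis sentence. Willingness to treat matches the willingness scale. Nothing in the sentence can stand for training or waiver. The rest turns on how the harm reduction phrase is read:

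| Reading of the phrase | Listed items named | Listed items not named | Unlisted items added |
|---|---|---|---|
| Loose label for both parts | willingness, knowledge, attitudes | training, waiver (2 of 5) | 0 |
| Attitudes matched, knowledge literal | willingness, attitudes | training, waiver, knowledge (3 of 5) | 1 |
| Literal for both parts | willingness | training, waiver, knowledge, attitudes (4 of 5) | 2 |

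Harm reduction occurs nowhere else in the documents, so nothing settles which reading is meant. Training and waiver are unnamed under all three.

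**2. Model for the yes/no items.** There are two possibilities.

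- The analysis sentence does not cover training and waiver. They then have no analysis.
- It covers them implicitly. They then inherit a paragraph that promises a suitable link but names only Gaussian with identity, for the feasibility outcomes.

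No binomial or logit model is named anywhere. Either way the model is not explicitly specified.

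**3. Waiver denominator.** Current prescribers below full capacity can enrol, and the adoption outcome confirms this by counting an enlarged existing patient panel. Section 4.1.a treats the waiver as a condition of prescribing. On the documents' own terms, current prescribers hold one. Define:

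- f₁, f₀: share already waivered at baseline in the intervention and control arms (not given);
- p₁, p₀: probability of a new waiver among those without one;
- c: how an already-waivered clinician is coded (0 or 1), the same in both arms.

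The proportion in arm a is fₐc + (1 − fₐ)pₐ. If f₁ = f₀ = f, the fc terms cancel:

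risk difference in everyone = (1 − f)(p₁ − p₀).

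For illustration only, with an assumed 10-point effect on new waivers:

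- f = 0.2: 10 × 0.8 = 8 points.
- f = 0.5: 10 × 0.5 = 5 points.

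If the shares differ and there is no effect (p₁ = p₀ = p), the difference is (f₁ − f₀)(c − p). This is generally not zero and can have either sign. Attenuation toward zero therefore depends on similar shares in the two arms.

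**4. Baseline values.** Section 4.1.a says participants are assessed at baseline, and the power section assumes differences-in-differences. The model paragraph names only the 3- and 6-month outcomes and no baseline term, so the scales would inherit an analysis without baseline adjustment.

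**5. Clinic term.** Arm is assigned to whole clinics, four to intervention and two to control. The arm indicator is the sum of the four intervention-clinic indicators. With all clinics fitted as fixed effects, the arm column adds nothing to the design matrix, and an overall arm effect cannot be separated from the clinic effects. Any outcome sent to this approach inherits that. With clinic as the unit of allocation, the between-clinic degrees of freedom are 6 − 2 = 4.

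**The case against.** The strongest reply is that this is an incomplete parenthesis. The table already fixes the outcomes, their form and their timing, the section heading covers secondary outcomes generally, and the phrase may be shorthand for the knowledge and attitude rows. That reading is possible, but the order of terms does not confirm it: the table puts knowledge before willingness and the analysis sentence reverses them. Even so, training and waiver remain unnamed.

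A reader might go further in four ways, and the documents do not support any of them.

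- *The plan would fit a Gaussian model to the yes/no items.* The Gaussian sentence is limited to the feasibility outcomes, a suitable link is promised in the same paragraph, and the Initial Data Inspection section says the data will inform the choice of a valid analysis. Nor can one hold both that the items are left out of the approach and that the approach assigns them a model. An identity-link model with robust errors would in any case estimate a risk difference for a binary outcome. The defect is under-specification.
- *Exactly three of five items are missing and one is added.* That requires reading attitudes loosely and knowledge literally within one phrase. The supportable statement is two to four.
- *The waiver effect loses 20 to 50% of its size.* Neither those shares nor a 10-point effect is in the documents, and with only two control clinics the shares may differ by arm.
- *The unnamed items will go unanalysed.* The text leaves this open; it does not establish it.

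It is also fair to object that a restricted waiver analysis needs baseline waiver status, which the documents do not say is collected, and that random-effect models are fragile with six clinics. Both objections stand and are met in the fix.

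**Conclusion.** The concern holds in this form. The analysis section and the outcome table disagree on the secondary outcomes: training and X-waiver are unnamed on every reading, and between two and four of five items are unnamed overall. The two yes/no items have no explicit model. The waiver outcome, analysed in everyone, includes clinicians who cannot newly receive a waiver. Its risk difference is scaled by (1 − f) if f is similar across arms and already-waivered clinicians are coded alike; f is unknown.

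The mismatch and the missing model need no assumption beyond the text. The waiver point rests on the documents' own statement that the waiver is needed to prescribe. These are secondary outcomes in a pilot and no sample-size or power figure changes, so the matter should be corrected before analysis but does not threaten the trial.

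**What to change.** - In the section on analyses of secondary outcomes, replace the parenthesis with the table's five items by the table's names: additional training, X-waiver, prescribing knowledge, willingness, attitudes toward patients with OUD.
- Delete harm reduction, or add it to the table with its instrument and time frame.
- State distribution and link for each outcome, with a binomial model for training and waiver.
- Define the waiver outcome as a new waiver among clinicians without one at baseline, and record waiver status in the baseline survey.
- Adjust the knowledge, willingness and attitude scales for their baseline values.
- Replace the clinic fixed effect with a clinic random effect, or treat clinic as the cluster, in either case with a small-sample correction suited to six clinics.

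Cost: mostly SAP wording, plus a baseline survey item if waiver status is not already asked. The waiver analysis will have a smaller denominator. Moving clinic from fixed to random or cluster is a change of model rather than of wording, and the small-sample correction will give wider intervals than an analysis that ignores clustering. The sample size is unaffected.

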#### **Missing data:**

Strategies to minimize loss to follow-up and missing data will be undertaken in partnership with the Ohio Association of Community Health Centers who are partnering to recruit and retain participants in the study.

207 For any outcome, if we are missing >10% of observations, we will assess predictors of loss to follow-up and  
208 apply multiple imputation under the assumption that data are missing at random (MAR) conditional on  
209 observed data. When disseminating results, we will present both complete-case and imputed results along  
210 with a description of the accompanying assumptions.  
211
